**Fig. 1 Fig1:**
[figure not shown]
Study design of the PHARM-NUDGE study

### Patient education

The pharmacists responsible for patient education in the PHARM-NUDGE study use special educational tools that incorporate nudge strategies and provide skincare education to patients assigned to the nudge-based education group at visit 1. We prepared two types of educational tools that incorporate several nudges and simplified messages, tailored to the specific features of different skin toxicities (Fig. 2). One tool is designed for patients scheduled to receive chemotherapy regimens containing capecitabine, liposomal doxorubicin, or lenvatinib, which are strongly associated with HFS or hand–foot skin reaction. The other tool is prepared for patients scheduled to receive chemotherapy regimens containing cetuximab or panitumumab, which are strongly associated with acneiform rash. Example sentences from our educational tools, along with their respective nudge types, are presented in Table 2. Patients assigned to the standard education group receive skincare education using the actual tools and explanations used in daily clinical practice at each study institution. In our study design, patients assigned to the nudge-based education group will receive additional explanatory materials on measures to prevent and manage skin toxicities, in addition to general information materials about chemotherapy. To avoid any effects on outcomes from distributing the additional materials themselves, independent of the nudge elements, we also provided patients in the standard education group with supplementary materials on skin toxicities that did not include any nudge elements (Supplementary Fig. S1). Additionally, to minimize differences in educational content and time spent between the two groups, we plan to provide pharmacists responsible for patient education with prior instruction on key points and time allocation.

**Fig. 2 Fig2:**
[figure not shown]
Educational tools that incorporate nudge strategies. Two educational tools were prepared. One tool is designed for patients scheduled to receive chemotherapy regimens containing capecitabine, liposomal doxorubicin, or lenvatinib, which are strongly associated with hand–foot syndrome (HFS) or hand–foot skin reaction (HFSR). The other tool is prepared for patients scheduled to receive chemotherapy regimens containing cetuximab or panitumumab, which are strongly associated with acneiform rash. The Japanese-language version is used in the actual study

**Table 2 Tab2:** Example sentences from our educational tools and their respective nudge types

Nudge type	Sentence
**“Loss aversion”**: People tend to be more sensitive to potential losses or harm than to gains.	“Unless the following preventive measures are taken, your skin cannot be protected from side effects!”
	“A previous study reported that the incidence of skin side effects may more than double in the absence of moisturizing and other preventive care.”
	“Moisturizing becomes less effective if more than 10 minutes pass after bathing.”
	“Water temperatures above 40 °C may increase your risk of skin side effects.”
**“Watching eye effect”**: People tend to change their behavior when they feel they are being observed.	“Your adherence to the following preventive measures will be checked at your next visit.”
**“Social norms”**: People tend to follow what others do.	“Most patients receiving skin-toxic chemotherapy can achieve good preventive effects by taking the following measures.”
	“Most patients in our hospital actually moisturize at least twice a day.”

### Primary endpoint

In the PHARM-NUDGE study, five behavioral criteria are predefined (Table 3). The primary endpoint, defined based on expert consensus among six specialized pharmacists, including Board certified Senior Oncology Pharmacists, is the proportion of patients who meet four or more of the five behavioral criteria in each group. We also estimate 95% confidence intervals (CIs) for the proportions of the two groups.

**Table 3 Tab3:** Predefined behavioral criteria for evaluating patients’ self-care behaviors

Behavioral criteria for patients scheduled to receive a chemotherapy regimen containing capecitabine, liposomal doxorubicin, or lenvatinib
1. The behavior of moisturizing at least twice a day
2. The behavior of setting the shower or bath temperature to lukewarm (38–40°C)
3. The behavior of applying moisturizers within 10 minutes after bathing
4. The behavior of avoiding irritation of the hands (e.g., by wearing protective [rubber] gloves during housework or outdoor activities)
5. The behavior of avoiding irritation of the feet (e.g., by wearing thick socks and avoiding prolonged walking)
**Behavioral criteria for patients scheduled to receive a chemotherapy regimen containing cetuximab or panitumumab**
1. The behavior of moisturizing at least twice a day
2. The behavior of setting the shower or bath temperature to lukewarm (38–40°C)
3. The behavior of applying moisturizers within 10 minutes after bathing
4. The behavior of avoiding wearing tight-fitting clothing or shoes
5. The behavior of avoiding direct sunlight (ultraviolet exposure) when going outside by using sunscreen, a parasol, a hat, and wearing long-sleeved clothing and long pants

### Secondary endpoint

Five secondary endpoints are predefined: (1) self-implementation rates for each behavioral criterion described in Table 3; (2) the absolute difference between the two groups in the proportion of patients who achieve the primary endpoint; (3) visual analog scale scores for changes in patients’ motivation to perform self-skincare behaviors after pharmacist-led education; (4) incidence rates of dermatological adverse events of grade ≥2 according to the Common Terminology Criteria for Adverse Events 6.0 [10]; and (5) the rate of self-purchase of moisturizers by participants in the absence of a prescription from medical institutions.

### Sample size calculation

In the PHARM-NUDGE study, the target enrollment is a minimum of 120 participants. The sample size is determined by considering 95% CIs for the population proportion of the primary endpoint. The 95% CIs for the population proportion are calculated using the Wald method as follows: 1$${\hat p \pm 1.96 \times \sqrt {\frac{{\hat p\left( {1 - \hat p} \right)}}{n}} }$$

where *p*^*^*^ is the observed proportion and *n* is the sample size.

Assuming that 70 out of 80 participants achieve the primary endpoint in the nudge-based education group, the implementation rate and 95% CI are 0.88 and 0.80 to 0.95, respectively. In the standard education group, if 20 out of 40 participants achieve the primary endpoint, the implementation rate and 95% CI are 0.50 and 0.35 to 0.65, respectively. Based on these assumptions, the difference in the implementation rates between the two groups is 0.38 (95% CI, 0.20–0.55), which is calculated using the following formula based on the Wald method: 2$${\left( {{{\hat p}_1} - {{\hat p}_2}} \right) \pm 1.96 \times \sqrt {\frac{{{{\hat p}_1}\left( {1 - {{\hat p}_1}} \right)}}{{{n_1}}} + \frac{{{{\hat p}_2}\left( {1 - {{\hat p}_2}} \right)}}{{{n_2}}}} }$$

where *p*^*^*^_*1*_ and *p*^*^*^_*2*_ denote the observed proportions in the two groups, and *n1* and *n2* denote the respective sample sizes.

### Subgroup analyses

Stratified analyses will be performed by sex, chemotherapy regimen, cancer type, prior treatment status, enrollment institution, and the pharmacist who provides patient education.

### Data collection and management

The five behavioral criteria are assessed at Visit 2 through interviews conducted by pharmacists who have received prior training. Changes in patients’ motivation to perform self-skincare behaviors after pharmacist-led education are evaluated using visual analog scales at Visit 2. Incidence rates of dermatological adverse events are monitored by the attending physicians from Visit 1 to Week 8. The rate of self-purchase of moisturizers by participants is assessed at Visit 2 through interviews conducted by pharmacists. We have a data monitoring committee at Hamamatsu University Hospital (Hamamatsu, Japan) that is independent of the pharmacists responsible for data collection. Data collected at each study site are centralized and managed by the data monitoring committee through an electronic data capture system.

### Statistical analysis

Standardized mean differences will be used for between-group comparisons of patient baseline characteristics. CIs for the proportion of patients achieving the primary endpoint in each group will be calculated using *Formula 1*. CIs for the absolute difference between the two groups in the proportion of patients who achieve the primary endpoint will be calculated using *Formula 2*. Between-group comparisons for continuous variables will be performed using *t*-tests or Mann–Whitney *U* tests. Group comparisons for categorical variables will be conducted using chi-square tests or Fisher’s exact tests. *p* values < 0.05 are considered statistically significant.

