### Study design

An overview of the PHARM-NUDGE study is presented in Fig. 1. The enrolled patients are randomly assigned in a 2:1 ratio to the nudge-based education plus standard education or standard education alone groups. Randomization is performed using block sizes of three and six, which vary randomly, and is stratified according to the cancer chemotherapy regimen administered to each patient. Two study visits are scheduled for each participant: visit 1 on the first day of the chemotherapy regimen and visit 2 on the day of the second administration. At visit 1, each participant receives pharmacist-led education on preventive skincare practices depending on their assigned group (nudge-based education plus standard education or standard education alone). Patients’ self-care behaviors at home are assessed at visit 2. After enrollment, all participants are followed for eight weeks to assess skin toxicity.

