In the PHARM-NUDGE study, randomization is performed using the stratified permuted block method with a 2:1 allocation ratio. Stratified randomization is reasonable for small trials in which treatment outcomes may be affected by known clinical factors [11]. In our trial, the chemotherapy regimen administered to each participant was selected as a stratification factor because it is strongly associated with cancer type, sex, age, and the incidence of dermatological adverse events, all of which may create heterogeneity in the environment and influence patients’ behavioral decisions. The allocation ratio was set at 2:1 to ensure that a larger number of participants are assigned to the nudge-based education group to obtain a more precise 95% CI estimate for this group. The PHARM-NUDGE study was designed not primarily to demonstrate the superiority of nudge-based education over standard education, but to accurately estimate the effect size of nudge-based education in the target population.

In this trial, we prepared special educational tools that incorporate nudge-based approaches (Fig. 2 and Table 2). Loss aversion, a fundamental concept in behavioral economics, refers to the tendency for people to be more sensitive to potential losses than to equivalent gains [12]. A representative example of loss aversion is vaccination promotion. Wang et al. showed that loss-framed messaging significantly increases COVID-19 vaccine acceptance [13]. The watching eye effect is a psychological phenomenon whereby people are more likely to engage in prosocial behaviors when they feel that others are watching them. Gaube et al. showed that visual eye cues improved hand hygiene compliance among healthcare workers [14]. In the PHARM-NUDGE study, although visual eye cues are not used, the educational tools clearly state that patients’ self-care behaviors at home would be checked at their next visit, thereby creating a psychological sense of being observed by healthcare workers. Social norms refer to individuals’ tendency to follow behaviors that are common or expected within a group. For example, telling adolescents with epilepsy how well their peers took their medications increased adherence [15]. Loss aversion, watching eye effects, and social norms have been established as nudge-based approaches, and their effectiveness is anticipated in the PHARM-NUDGE study.

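### Randomisation is stratified by chemotherapy regimen, but the confidence interval for the between-group difference is fixed as an unstratified Wald formula, so it is conservative if regimen predicts the endpoint

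*Protocol article*

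**What the plan says.** - **Randomisation.** Under Study design, "The enrolled patients are randomly assigned in a 2:1 ratio" with blocks of three and six, and allocation "is stratified according to the cancer chemotherapy regimen administered to each patient".
- **Reason for stratifying.** The Discussion says "the chemotherapy regimen administered to each participant was selected as a stratification factor because it is strongly associated with cancer type", as well as sex, age and the incidence of dermatological adverse events, "all of which may create heterogeneity in the environment and influence patients’ behavioral decisions".
- **Analysis of the difference.** Under Statistical analysis, "CIs for the absolute difference between the two groups in the proportion of patients who achieve the primary endpoint will be calculated using" Formula 2. The Sample size calculation section gives that formula as the plain two-sample Wald interval. The tests named for categorical variables, chi-square or Fisher's exact, are also unstratified.
- **Status of the difference.** Under Secondary endpoint, item (2) is "the absolute difference between the two groups in the proportion of patients who achieve the primary endpoint". The primary endpoint is the proportion in each group separately.
- **Other use of regimen.** Under Subgroup analyses, "Stratified analyses will be performed by sex, chemotherapy regimen, cancer type" and further factors. These give results within subgroups, not a regimen-adjusted overall difference.

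**The concern.** When allocation is balanced within strata that predict the outcome, variation between strata largely cancels out of the treatment comparison. A variance formula built on pooled proportions still counts that variation, so it overstates the standard error. The analysis then does not match the design.

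The article gives grounds for expecting success rates to vary by regimen, without showing that they do. The Discussion raises the possibility. In Table 3, criteria 4 and 5 differ between the hand–foot drugs and cetuximab or panitumumab. The survey cited in the Background reports 74.1% adherence for moisturiser use and 14.1% for sunscreen, and sun protection is a criterion only in the second group.

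At stake is the width of one interval. No power target is stated and the design rests on precision, so that width is much of what the trial delivers on its stated objective of estimating the incremental effect of nudges.

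**Working it through.** **1. The plan's own figures.** The inputs come from the Sample size calculation section, where "the target enrollment is a minimum of 120 participants": 70/80 = 0.875 and 20/40 = 0.50.

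Formula 2: 0.375 ± 1.96 × √(0.875×0.125/80 + 0.50×0.50/40) = 0.375 ± 1.96 × √(0.001367 + 0.006250) = 0.375 ± 0.171, i.e. 0.204 to 0.546. This reproduces the stated 0.38 (0.20–0.55).

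**2. Stratified variance.** With stratum shares w, within-stratum rates p1 and p2, and 2:1 balance within each stratum, the variance is Σ w × [p1(1−p1)/80 + p2(1−p2)/40]. The shares and within-stratum rates are assumptions, because the article gives none. All are set to keep the overall rates at about 0.875 and 0.50.

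Worked example with two strata (shares 0.625 and 0.375; nudge 0.95 and 0.75; standard 0.65 and 0.25):
- Overall nudge: 0.625×0.95 + 0.375×0.75 = 0.875. Overall standard: 0.625×0.65 + 0.375×0.25 = 0.50.
- Nudge term: (0.625×0.0475 + 0.375×0.1875)/80 = 0.1000/80 = 0.001250.
- Standard term: (0.625×0.2275 + 0.375×0.1875)/40 = 0.2125/40 = 0.005313.
- Half-width: 1.96 × √0.006563 = 0.159 against 0.171, about 7% narrower.

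**3. Range of assumed associations.** The half-widths use the formula in step 2. Coverage comes from 5,000 simulated trials per row (N = 120, 2:1, blocks of 3 and 6 within strata, regimen mix drawn at random). The adjusted interval there is a stratum-adjusted linear risk difference with robust standard error. Monte Carlo error is about ±0.6 points (1.96 × √(0.95×0.05/5000)).

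| Assumed association (standard-arm rates) | Stratified half-width | Narrower than Formula 2 | Formula 2 coverage | Adjusted coverage |
|---|---|---|---|---|
| None | 0.171 | 0% | 94.4% | 94.5% |
| Mild (0.38 to 0.58) | 0.168 | 1.7% | 93.8% | 93.8% |
| Moderate (0.34 to 0.62) | 0.166 | 2.8% | 94.1% | 93.7% |
| Strong (0.20 to 0.75) | 0.152 | 11.5% | 95.9% | 93.8% |
| Extreme (0.20 vs 0.80) | 0.141 | 17.4% | 97.6% | 94.8% |

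Simulating the two-stratum example of step 2 with a Mantel-Haenszel interval gave mean half-widths of 0.169 (Formula 2) and 0.161, about 5% narrower (1 − 0.161/0.169), and coverage of 95.7% and 94.7%. A separate simulation of the extreme case put Formula 2 coverage at 97.3%.

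**4. Is the estimate itself less precise?** No. In the two-stratum example the simulated standard deviation was 0.0812 for the unstratified difference and 0.0811 for the Mantel-Haenszel difference. In the strong case, 1.96 × SD was 0.156 and 0.155. Bias was about zero for both. Stratified blocking delivers the gain whichever estimator is used. Formula 2 only fails to report it.

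**The case against.** The strongest case against is that little turns on this. The difference is a secondary endpoint, the Discussion says the trial was not primarily designed to show superiority, and no decision rule depends on the interval. Any error is conservative. For mild or moderate association Formula 2 covers about as well as the adjusted interval, because its slight excess width offsets the Wald method's small-sample undercoverage. With five equal strata and standard-arm rates from 0.7 to 0.3 (nudge rates assumed 0.95 to 0.80), coverage was 94.8% for Formula 2 and 94.5% for Mantel-Haenszel. The advantage appears only when regimens differ widely, and those rates are invented. All of this stands, and it limits the point to a low-cost improvement.

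It can also be said that a supplementary adjusted estimate is the kind of detail a separate analysis plan holds. That answers less well. The article is not silent on the method: it names the unstratified formula for this interval. The planned subgroup results by regimen do not supply an overall stratified estimate.

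**Conclusion.** The mismatch between stratified randomisation and the unstratified interval is explicit in the article and worth correcting. Its effect is modest and in the safe direction: an interval 0–3% too wide under weak to moderate association, and about 5–17% too wide under strong association, with Formula 2 coverage from about 94% up to about 97%. These sizes rest on assumed regimen-specific rates and on the planning rates of 0.875 and 0.50.

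Four stronger readings are tempting, and the documents do not support them:
- **That the trial loses precision, or in effect needs more patients.** In the two-stratum example the ratio of the two variance formulas is 0.007617/0.006563 = 1.16. A reader might take that as 16% of the sample wasted. It is a ratio of reported variances, and the estimators' actual standard deviations are nearly identical.
- **That the primary analysis is at fault.** The primary endpoint is each group's own proportion; the difference is secondary.
- **That the protocol says regimen determines behaviour.** The Discussion says only that factors linked to regimen may influence it.
- **That institution must also be adjusted for, because the standard arm uses each site's own materials.** Institution is not a randomisation stratum, so this mismatch gives no ground for it.

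**What to change.** In the Statistical analysis section, make a regimen-stratified Mantel-Haenszel (or standardised) risk difference with a stratified 95% confidence interval the main between-group estimate for secondary endpoint (2). Use the randomisation strata, with a prespecified rule for pooling sparse regimens, for example into the two educational-tool groups. For grade ≥2 skin toxicity, use the Cochran-Mantel-Haenszel analogue, since the article itself links regimen to the incidence of these events. Keep Formula 2 as a sensitivity analysis, so the planning calculation remains traceable.

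The cost is a change of wording and a few lines of code. Regimen is already recorded for randomisation, so no new data and no change in sample size are needed. Enrolment began on October 15, 2025, so the change should be fixed before outcome data are analysed by group.

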## Discussion

The PHARM-NUDGE study is a multicenter, randomized, parallel-group, single-blind, controlled trial designed by pharmacists to evaluate the potential benefits of integrating nudge strategies into patient education. Patient enrollment started on October 15, 2025, and includes patients scheduled to receive cancer chemotherapy regimens that are strongly associated with dermatological adverse events. Although the effect of nudge strategies on promoting desirable behaviors has been demonstrated in various fields, including healthcare, there is no robust evidence on whether nudge-based, pharmacist-led education can promote patients’ preventive behaviors against skin toxicities associated with cancer chemotherapy. To the best of our knowledge, this is the first prospective interventional study with the potential to fill this evidence gap, and the completion of the trial and acquisition of the final results are eagerly anticipated.

Many anticancer drugs have been reported to be associated with skin toxicities. In the PHARM-NUDGE study, we prospectively enroll patients scheduled to receive a chemotherapy regimen containing capecitabine, liposomal doxorubicin, lenvatinib, cetuximab, or panitumumab in outpatient chemotherapy units or during hospitalization. These anticancer drugs are known to cause HFS, hand–foot skin reaction, and acneiform rashes [2]. They are also key components of several chemotherapy regimens routinely administered in outpatient chemotherapy units, including capecitabine plus oxaliplatin and lenvatinib plus pembrolizumab. Based on our preliminary survey of prescription practices at each study site (data not shown), we expected that the majority of the enrolled patients would be outpatients. To minimize the additional time burden on outpatient participants, we planned to provide patient education during intravenous administration in outpatient chemotherapy units. Given these practical considerations, we did not include patients receiving single-agent oral anticancer therapy (including regorafenib, sunitinib, or osimertinib) because it would have been difficult for hospital pharmacists to secure sufficient time for education in cases without infusion therapy in outpatient chemotherapy unit or during hospitalization. Therefore, the five drugs were selected as target agents because they are frequently prescribed at the participating institutions and are commonly used in combination with intravenous anticancer drugs.

In the PHARM-NUDGE study, randomization is performed using the stratified permuted block method with a 2:1 allocation ratio. Stratified randomization is reasonable for small trials in which treatment outcomes may be affected by known clinical factors [11]. In our trial, the chemotherapy regimen administered to each participant was selected as a stratification factor because it is strongly associated with cancer type, sex, age, and the incidence of dermatological adverse events, all of which may create heterogeneity in the environment and influence patients’ behavioral decisions. The allocation ratio was set at 2:1 to ensure that a larger number of participants are assigned to the nudge-based education group to obtain a more precise 95% CI estimate for this group. The PHARM-NUDGE study was designed not primarily to demonstrate the superiority of nudge-based education over standard education, but to accurately estimate the effect size of nudge-based education in the target population.

In this trial, we prepared special educational tools that incorporate nudge-based approaches (Fig. 2 and Table 2). Loss aversion, a fundamental concept in behavioral economics, refers to the tendency for people to be more sensitive to potential losses than to equivalent gains [12]. A representative example of loss aversion is vaccination promotion. Wang et al. showed that loss-framed messaging significantly increases COVID-19 vaccine acceptance [13]. The watching eye effect is a psychological phenomenon whereby people are more likely to engage in prosocial behaviors when they feel that others are watching them. Gaube et al. showed that visual eye cues improved hand hygiene compliance among healthcare workers [14]. In the PHARM-NUDGE study, although visual eye cues are not used, the educational tools clearly state that patients’ self-care behaviors at home would be checked at their next visit, thereby creating a psychological sense of being observed by healthcare workers. Social norms refer to individuals’ tendency to follow behaviors that are common or expected within a group. For example, telling adolescents with epilepsy how well their peers took their medications increased adherence [15]. Loss aversion, watching eye effects, and social norms have been established as nudge-based approaches, and their effectiveness is anticipated in the PHARM-NUDGE study.

The primary endpoint of the PHARM-NUDGE study was defined according to the behavioral criteria for assessing patients’ self-care behaviors (Table 3). Using moisturizers and avoiding skin irritation are recommended as basic self-care measures in clinical practice guidelines [4, 5]. Therefore, it is important to encourage patients to engage in these behaviors. However, evidence demonstrating that these behaviors can prevent skin toxicity remains inconclusive. A randomized phase III study evaluated the effect of a structured teaching model incorporating intensive prophylactic measures (including routine use of emollients three to four times a day and wearing loose-fitting clothes and shoes) on the prevention of capecitabine-induced HFS; however, the intervention did not demonstrate a statistically significant difference [16]. Although our trial included the incidence of dermatological adverse events as a secondary endpoint, it may be challenging to detect a statistically significant difference between the two groups.

In the PHARM-NUDGE trial, our primary objective is to estimate the incremental effect of integrating nudge-based strategies into standard patient education. To ensure standardization of baseline educational practices, responsibility for patient education was assigned to a single healthcare professional. Nevertheless, we believe that this nudge-based approach is not inherently limited to pharmacists and may be adaptable to other healthcare professionals in future implementations.

Our study protocol has potential limitations. Firstly, differences in the educational materials or in pharmacists’ explanations may allow participants to infer their assigned group. To address this issue, we plan to inform participants only that two types of educational approaches are being compared, without disclosing that a special educational tool will be provided exclusively to one group. Secondly, although we described the study design as a single-blind trial in the Methods section, it is not possible to fully blind the differences in the educational materials between the two groups. Therefore, it should be noted that the trial is not fully single-blinded.

